## Methods

### Design

The present pilot study is a double-blind, randomized, crossover clinical trial with two arms (Figs. 1 and 2, SPIRIT). Participants will be randomly assigned to either experimental intervention (GNPT^®^) or sham intervention (ictus.online). In the first phase, participants in group A will start with the experimental intervention over a 6-week period (30 sessions), and participants in group B will start with the sham intervention over the same 6-week period (30 sessions). Participants will connect from their homes with their computer to the assigned intervention (experimental intervention or sham intervention). It will be indicated to them to connect once a day, from Monday to Friday, for 6 weeks. After a 3-month washout period, the second phase will commence, in which the groups will be crossed over, namely group A will receive the sham intervention and group B will receive the experimental intervention for 6 weeks each.

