### Participants

Forty chronic-stage stroke patients with cognitive impairment involving alteration in attention, memory, and/or executive functions will be recruited. The sample will be composed of former patients of Institut Guttmann who have previously received cognitive rehabilitation in the sub-acute phase of evolution.

Recruitment will include postal, email, and telephone contact with participants. Participants will be informed about the study features, goals, and implications of their participation, the duration of the study and the type of procedures that will be applied. Informed consent will be obtained in order to include them in our database. After providing informed consent to participate, participants will schedule an appointment at our center for a baseline testing session.

Inclusion criteria for the trial are (1) age over 18 years old, (2) a stroke diagnosis (ischemic stroke or hemorrhagic stroke); (3) a time of evolution of 12 months or more since stroke occurred (chronic-stage); (4) cognitive impairment confirmed by pre-intervention neuropsychological assessment; and (5) willingness to give written informed consent to participate in the study. Exclusion criteria are (1) diagnosis of language deficits or aphasia; (2) motor impairment concerning upper limbs that may incapacitate them for computer use; (3) severe alteration of the visual field or perceptual problems; (4) health status that may require further intervention or admission to a medical center during the study; (5) neurological or psychiatric history; or (6) substance abuse.

A neuropsychological screen evaluation to check exclusion criteria (1) and (3) will be applied. It will consist of an orientation and language test (orientation, word-repetition, visual-naming, and order comprehension subtests of Test Barcelona-R) [25]. The cutoff needed to participate in the study is 100% proficiency on these tests.

In addition, we will recruit a next-of-kin for each participant, to whom we will administer questionnaires about the impact of attention, memory, and executive function impairment on the patient’s daily life at pre-training, post-training, and follow-up testing stages.

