#### Statistical analysis

##### Analysis

Data analysis will be based on the intention-to-treat principle, which means that all participants who were randomized will be included in the final analysis, regardless of their adherence to any of the interventions. To avoid the problems derived from missing data (no attendance to neuropsychological assessments), blank spots will be filled with missing data imputation technique last value carried forward.

In order to detect changes in the variables recorded for the primary outcome and secondary outcome, a within-subject comparison pre-/post-intervention in both groups after both interventions will be made, as well as comparisons between groups (group A and group B).

Our null hypothesis is that a difference between baseline scores (A1 for group A and A3 for group B) and scores post-treatment (A2 for group A and A4 for group B) will not be significantly different from zero. Therefore, the Kolmogorov–Smirnov test will be used to examine the data for normality, and either ANOVA (parametric test) or Kruskal–Wallis (non-parametric test) will be used to analyze the measurements. A significance level of 95% will be used (*P* < 0.05 cutoff). Demographic (age, sex, years of education) and etiologic characteristics (ischemic stroke or hemorrhage) will be described using descriptive statistics for each group (group A and group B). The Bonferroni method will be applied to adjust the overall level of significance for multiple outcomes.

Alternatively, composite indices will be created by transforming raw neuropsychological test scores into z scores using published normative data. Domains will be created by averaging the z scores for each test within the domain (M = 0; SD = 1). This system has been used before in similar studies [44, 45].

If the sample size of this pilot study allows, a longitudinal mixed model will be applied.

Data analysis will be performed by an analyst outside the study with the statistical analysis software R and appropriate packages (“lmm” and “psych”) [46].

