## Discussion

The first objective of this research is to study the effectiveness of a patient-customized computerized cognitive training program (GNPT^®^) as a home-based cognitive stimulation tool for stroke patients in the chronic stage of recovery. We hypothesize that training cognitive functions of attention, memory, and executive functions with GNPT^®^ could lead to better function of those cognitive domains post-therapy. Furthermore, we want to study whether customized cognitive training could lead to an improvement in other contexts different from the examination tests, improving performance in both related (near transfer) and unrelated (far transfer) tasks. Finally, we want to study the impact of variables such as demography and etiology on rehabilitation outcome.

The strengths of our study include that it is designed to (1) be easily replicated in new patient cohorts, (2) minimize unintended variability by reducing intervention heterogeneity, (3) adjust the type and difficulty of exercises to the specific cognitive impairment profile of patients, and (4) monitor adherence and performance of each exercise during the whole treatment.

Furthermore, our study focuses on targeting cognitive rehabilitation toward the improvement of the quality of life of the patient. In this sense, we include in our primary outcome measures an assessment of functioning in daily life, before, during, and after the performance of both interventions. Additionally, our design is longitudinal, which offers the possibility of studying the maintenance of the results over time (over 3 and 6 months). The timing of the primary outcome is 3 months. The purpose of the follow-up at 6 months is to check the evolution of patients once they have stopped receiving any type of intervention.

Furthermore, the execution of both interventions will be remotely monitored and we will be able to record the quantity and quality of the execution of the participants. Nevertheless, we consider a limitation the fact that we will not be able to control the environmental conditions in which participants perform the tasks. Another limitation is that the battery assessment will be the same throughout the study, which might create a learning effect and/or ceiling effect in some evaluation tasks.

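### The one stated null hypothesis is zero pre/post change over the GNPT periods, so rejecting it would not show benefit over sham

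*Protocol article*

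**What the plan says.** The Design section sets up a sham-controlled crossover: "Participants will be randomly assigned to either experimental intervention (GNPT^®^) or sham intervention (ictus.online"). Group A has GNPT first: "participants in group A will start with the experimental intervention over a 6-week period (30 sessions"). Group B starts with sham. After the washout, "group A will receive the sham intervention and group B will receive the experimental intervention for 6 weeks each".

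The Analysis section then gives a single null hypothesis, which opens: "Our null hypothesis is that a difference between baseline scores (A1 for group A and A3 for group B) and scores post-treatment". It goes on to name the later visits and the null value: "A2 for group A and A4 for group B) will not be significantly different from zero". The sentence before it plans further comparisons: "a within-subject comparison pre-/post-intervention in both groups after both interventions will be made, as well as comparisons between groups (group A and group B"). A longitudinal mixed model follows only if the sample size permits. Bonferroni is to be applied across outcomes.

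Two other statements bear on this. The Discussion lists as a limitation that "the battery assessment will be the same throughout the study, which might create a learning effect and/or ceiling effect in some evaluation tasks". Inclusion criterion 4 under Participants is "cognitive impairment confirmed by pre-intervention neuropsychological assessment".

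**The concern.** A sham arm is there to absorb whatever would change without the active treatment: familiarity with the tests, regression to the mean, attention from staff, time. It can do so only if the tested hypothesis contains it. The hypothesis as written contains only the changes made while on GNPT, so it is an uncontrolled before/after test inside a randomised trial.

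The article itself supplies two reasons why scores may rise without a GNPT effect. The same battery is used at every assessment, and patients enter because they score as impaired before treatment. If the stated null were rejected for those reasons, a retest gain could be reported as efficacy. The Sample size section says that the pilot's results will be used to plan a full-scale study. If the raw GNPT gain were used there as the effect size, that study would be too small.

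**Working it through.** **1. Which visits does the null use?**

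| Group | A1 to A2 | A3 to A4 |
|---|---|---|
| A | GNPT (in the null) | sham (not in the null) |
| B | sham (not in the null) | GNPT (in the null) |

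Reading the null instead as a comparison of group A's A1 to A2 change with group B's A3 to A4 change does not help, because both are GNPT periods.

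**2. What does group A versus group B estimate?** Let τ be the GNPT-minus-sham effect, and let π1 and π2 be the changes expected in each period without it. Assume no carryover.
- Group A: τ + π1 in period 1, π2 in period 2.
- Group B: π1 in period 1, τ + π2 in period 2.
- A minus B within period 1 is τ. Within period 2 it is −τ. Averaged over both periods it is 0.
- The stated null averages (τ + π1) and (τ + π2), giving τ + (π1 + π2)/2. With τ = 0 this is still (π1 + π2)/2.

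**3. How often is the stated null rejected when τ = 0?** The article has no power calculation to reproduce. Its 40 is 2 × 20, within the quoted guideline range of 24 to 70.

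Inputs from the article: n = 40, P < 0.05, Bonferroni. Nine primary measures are named (two for attention, three for memory, four for executive functions), so one possible Bonferroni level is 0.05/9 = 0.0056. The article does not fix the number of tests.

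Assumptions: two-sided test, complete data, average practice gain d in baseline SD units, retest correlation r. The test is a paired t-test, which equals a repeated-measures ANOVA with two time points.

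SD of change = √(2(1 − r)), which is 0.775 at r = 0.7 and 0.632 at r = 0.8. Noncentrality = d√40 / SD of change, with 39 degrees of freedom. For d = 0.2 and r = 0.7 it is 0.2 × 6.325 / 0.775 = 1.63, and the rejection probability is 36%.

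| Average gain d | At 0.05 (r = 0.7 / 0.8) | At 0.05/9, per outcome (r = 0.7 / 0.8) |
|---|---|---|
| 0 | 5% / 5% | 0.6% / 0.6% |
| 0.15 | 22% / 31% | 5% / 9% |
| 0.2 | 36% / 50% | 11% / 19% |
| 0.3 | 67% / 83% | 33% / 53% |

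**4. Smaller gain in period 2.** Group B's baseline is A3, its third testing, so its gain is probably smaller. A simulation (20,000 trials, 20 per group, r = 0.7, independent period changes, no carryover, τ = 0, level 0.05) gave:

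| Gain, period 1 / period 2 | Stated null | Period-adjusted GNPT minus sham | Period-1 A versus B |
|---|---|---|---|
| 0.2 / 0.1 SD | 22% | 5.1% | 5.1% |
| 0.3 / 0.15 SD | 44% | 4.8% | 5.0% |
| 0.4 / 0.2 SD | 66% | 4.7% | 5.0% |

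**5. Regression to the mean.** The article gives no impairment cutoff. If candidates were selected below a cutoff c (in SD units of the candidates' own distribution), the expected gain is (1 − r) × φ(c)/Φ(c). For c = 0 this is 0.798 × (0.2 to 0.3) = 0.16 to 0.24 SD. For c = −1 it is 1.525 × (0.2 to 0.3) = 0.31 to 0.46 SD. This would fall mainly on group A's A1 to A2 change, if A1 is the qualifying assessment. It is not included in the tables above.

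**The case against.** A reader might infer that the trial never compares GNPT with sham. The article does not support that. The sentence before the null plans pre/post comparisons after both interventions, so the sham changes are analysed. It also plans comparisons of group A with group B, and within the first phase that is exactly the randomised GNPT-versus-sham contrast, not merely a comparison of sequences. An article may also leave exact contrasts and model terms to a fuller document, so their absence is no fault here. All of this stands, and it limits the point to the hypothesis as worded. It does not rescue that wording. Separate pre/post tests under GNPT and sham do not test the difference between them, and a fuller plan built on GNPT minus sham would contradict the null printed here.

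The size also needs restraint. The upper figures assume equal gains in both periods and no Bonferroni correction. A smaller second-period gain and the planned correction both lower them, to about 5 to 9% per outcome for an average gain of 0.15 SD at 0.05/9. Three of the nine primary measures (RSAB, PRMQ, BRIEF-A) are rating questionnaires, for which a practice effect is less clear, and the Discussion expects learning only in some tasks. Regression to the mean is plausible for group A, but it cannot be sized from the article and is weaker for group B. Participants are former rehabilitation patients of the centre, so their impairment may not rest on A1 alone.

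Finally, this is an exploratory pilot that discloses the learning effect, and its 40 is not power-based. No sample-size figure in the article changes.

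**Conclusion.** The point holds for the null hypothesis as stated. It tests change during GNPT against zero, so its rejection is compatible with no benefit over sham. It does not hold as a claim that no randomised comparison is planned.

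With no GNPT-specific effect, an average practice gain of 0.15 to 0.3 SD would reject the stated null in 22 to 83% of trials at 0.05 (nominal 5%). At 0.05/9 it would do so in about 5 to 53% per outcome (nominal 0.6%). Smaller second-period gains move the result toward the lower end. These figures rest on n = 40, a two-sided test and an assumed retest correlation of 0.7 to 0.8, and the article gives neither that correlation nor the practice gain. Bonferroni reduces the rates but does not cure the problem, because the cause is bias and not multiplicity. That the hypothesis omits sham depends on none of these assumptions.

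**What to change.** Restate the null as: the mean difference between change under GNPT and change under sham is zero. Estimate it within participant and adjusted for period, as half of [(period-1 change minus period-2 change) in group A minus the same quantity in group B]. In the notation above this is ½[(τ + π1 − π2) − (π1 − τ − π2)] = τ, so the period effects cancel.

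State that this estimator assumes no carryover across the washout. Report the first-period difference in change between groups A and B as a check that does not need that assumption. Keep the pre/post changes within each condition as descriptive results.

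The cost is one paragraph of wording and no new data. The downside is that the reported effect is expected to be smaller than the raw pre/post gain, and the first-period check uses only half of the data.

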The second objective is focused on generalization, namely the ability to use what has been learned in rehabilitation contexts and apply it in different environments [15]. Transfer of learning is included within the concept of generalization when specifically referring to the ability to apply specific strategies to related tasks [16]. Two types of transfer have been proposed – near transfer and far transfer [17]. By near transfer we mean that, through the training of a task within a given cognitive domain, improved function in other similar, untrained tasks may be observed in the same cognitive domain. For instance, a patient who performs selective attention exercises and improves execution through the training might improve their performance in other selective attention exercises too. By far transfer we mean that training in a given cognitive domain may improve performance of tasks in other cognitive domains. Such improvement will be observable in tasks that are structurally dissimilar from the ones used in the training. For instance, if a patient performs selective attention exercises, they may also improve their performance in memory tasks.

It has been demonstrated that computerized cognitive training can lead to the phenomenon of transfer, as previously studied in stroke patients [18]. Thus, our research aims to note whether the application of patient-customized tele-rehabilitation can give rise to an improvement in other functions that are based on cognitive domains related to those that have been trained (near transfer) as well as in different ones (far transfer).

Finally, the third objective is to assess the variables of demography (age, sex, years of education) and etiology (ischemic stroke or hemorrhage) and their impact on rehabilitation outcome, given the need to understand the patient characteristics that may influence treatment effectiveness [19].

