### Sample size

This is study will be an explorative pilot study. The total sample size required for a two-arm trial following some currently proposed approximation guidelines is between 24 and 70 [21]. Some recently published studies similar to this one have used sample sizes within this range [22–24]. The aim is to recruit 40 participants (*n* = 20 per group). The results of this pilot study will be used to compute sample size and conduct a power calculation to plan a full-scale study.

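### The named tests are not tied to within-participant differences or to period, the stated null omits sham, and the mixed model that fits the crossover is optional

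*Protocol article*

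**What the plan says.** The Design section describes a "double-blind, randomized, crossover clinical trial with two arms", and adds: "After a 3-month washout period, the second phase will commence, in which the groups will be crossed over". The same people are assessed at A1 to A4 around the two treatment periods and again at A5. On size, "The aim is to recruit 40 participants", 20 per group.

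The Analysis section promises a within-subject pre/post comparison and comparisons of group A with group B. Its null hypothesis is that the change from A1 to A2 (group A) and from A3 to A4 (group B) is zero. In both groups that is the GNPT period. A normality check comes first: "the Kolmogorov–Smirnov test will be used to examine the data for normality". Its result then decides which of two test families applies: "either ANOVA (parametric test) or Kruskal–Wallis (non-parametric test) will be used to analyze the measurements". Last: "If the sample size of this pilot study allows, a longitudinal mixed model will be applied".

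The Discussion lists as a limitation that the same battery is used throughout and may produce learning. The Sample size section gives no effect size, SD or power.

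**The concern.** Three things do not fit together.

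- **Pairing.** The null concerns change in the same patients. Kruskal–Wallis compares independent groups, so on raw pre and post scores it cannot give the within-subject comparison that the same section promises. The parametric branch says only ANOVA, without a participant term.
- **Period and sham.** The null is about GNPT alone. If scores rise because the battery is repeated, a pre/post test credits that rise to GNPT. The sham period exists to remove it, but no named test carries a period or sequence term.
- **The suitable method is optional.** The mixed model depends on the sample size, and no threshold is given.

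At stake are the precision for which a crossover is chosen and the ability to tell training from practice. The estimates also matter later: "The results of this pilot study will be used to compute sample size and conduct a power calculation to plan a full-scale study".

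**Working it through.** **Inputs from the Protocol article:** 20 participants per sequence, 40 in all; assessments A1 to A4; significance level 0.05 (taken as two-sided). There is no power figure to reproduce; 2 × 20 = 40 agrees with the target and lies in the cited range of 24 to 70.

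**Assumptions, not in the documents:** SD 1 at each assessment; the same correlation r between all assessments, 0.5 to 0.9; a GNPT gain of 0.5 SD where power is computed; a practice gain of 0.3 SD at the second assessment and a further 0.15 SD by the fourth (0.45 SD in total) where practice is studied.

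**Step 1: pairing.** The true standard error of the mean pre/post change in 40 patients is √(2(1−r)/40): 0.158 at r = 0.5 and 0.071 at r = 0.9. An unpaired test uses √(2/40) = 0.224 whatever r is, so its statistic is too small by a factor √(1−r). At r = 0.5 a nominal critical value of 1.99 acts like 1.99/√0.5 = 2.81.

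For the paired test, 0.5/0.158 = 3.16 at r = 0.5, which on 39 degrees of freedom gives power of about 0.87.

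**Step 2: practice.** With no GNPT effect, group A changes by 0.30 SD (A1 to A2) and group B by 0.15 SD (A3 to A4), a mean of (0.30 + 0.15)/2 = 0.225 SD. At r = 0.5, 0.225/0.158 = 1.42, so a paired test of the stated null rejects about 28% of the time.

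**Step 3: the crossover contrast.** Take A2 − A4 in each participant and compare groups A and B. Practice shifts both groups alike and cancels. Half the difference in group means estimates GNPT minus sham, with standard error ½ × √(2(1−r)) × √(1/20 + 1/20) = √(2(1−r)/40). That is the same as for the paired test.

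**Step 4: simulation**, 4,000 runs per setting.

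| | r = 0.5 | 0.7 | 0.8 | 0.9 |
|---|---|---|---|---|
| Type I error, unpaired ANOVA | 0.009 | 0.000 | 0.000 | 0.000 |
| Type I error, unpaired Kruskal–Wallis | 0.012 | 0.002 | 0.000 | 0.000 |
| Type I error, paired t | 0.059 | 0.050 | 0.051 | 0.049 |
| Type I error, crossover (post scores) | 0.051 | 0.051 | 0.052 | 0.047 |
| Power, unpaired ANOVA | 0.65 | 0.66 | 0.71 | 0.74 |
| Power, unpaired Kruskal–Wallis | 0.61 | 0.63 | 0.67 | 0.72 |
| Power, paired t | 0.86 | 0.98 | 0.998 | 1.00 |
| Power, crossover (post scores) | 0.87 | 0.98 | 0.998 | 1.00 |
| Practice only: paired t rejects | 0.27 | 0.42 | 0.59 | 0.87 |
| Practice only: unpaired ANOVA rejects | 0.087 | 0.044 | 0.022 | 0.005 |
| Practice only: crossover rejects | 0.052 | 0.052 | 0.048 | 0.052 |

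The paired t-test has exact size 0.05 here, so 0.059 is simulation noise; 0.86 against 0.87 and 0.27 against 0.28 are noise as well. A crossover test on change scores also holds its level but has less power: 0.59, 0.79, 0.93 and 0.999.

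**Step 5: the normality gate.** Choosing the test by Kolmogorov–Smirnov left the unpaired type I error at 0.000 to 0.009. Uncorrected for estimated mean and SD, the gate flags exponential data in 4% of samples at n = 20 and 23% at n = 40. With the Lilliefors correction the figures are 60% and 90%. The article does not say which version is meant.

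**The case against.** The strongest reply is that the section promises a within-subject comparison and phrases its null as a difference. ANOVA may therefore mean repeated-measures ANOVA, or the tests may be run on change scores. This stands in part. On change scores grouped by treatment, simulated type I error was 0.043 to 0.058, close to nominal under the equal-correlation assumption. The harm depends on a choice that the text leaves open, and even this charitable reading supplies no period term.

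A reader might infer more than the article supports:

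- *That Kruskal–Wallis is wrong however it is used.* With two groups it is the rank-sum test. Comparing groups A and B on within-participant period differences, it had type I error of 0.049 to 0.050 and power of 0.85 (r = 0.5) and 0.97 (r = 0.7).
- *That sham is never compared.* Comparisons between groups are promised; sham is absent from the stated null, not from the plan.
- *That the mixed model could be chosen on the results.* Sample size is known without looking at outcomes, and the analyst is outside the study. The fault is the missing criterion.
- *That a wrong SD will go to the full-scale trial.* The article does not say which SD will be used, and any SD can be computed from the same data.
- *That the third objective goes untested.* The article says that "the third objective is to assess the variables of demography (age, sex, years of education) and etiology" and mentions only descriptive statistics by group. Interaction terms are commonly left to a fuller document, so this is a separate matter.

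It is also fair that model terms often wait for an analysis plan. But this article does name its tests and its null, and those are what fit the design badly.

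**Conclusion.** The point holds in this form: the article fixes a GNPT-only pre/post null and two test families without tying them to within-participant differences or to period, and it makes the design-appropriate model conditional on an undefined criterion.

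The size depends on the reading. Without pairing, the error is conservative: type I error of about 0.01 or less, and power of about 0.61 to 0.74 instead of 0.87 to 1.00 for a 0.5 SD gain. With pairing but no sham and period contrast, it is anti-conservative: about 28% to 87% false positives under the assumed practice gain. One cannot say flatly that the trial's error rates will be wrong, because some permitted readings are close to nominal. All these figures rest on assumed correlations, effects and practice gains.

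The Kolmogorov–Smirnov gate is secondary. It makes the choice of test data-dependent but hardly changed the error rates. Because the trial is an exploratory pilot with no power claim, this should be fixed, but it does not invalidate the trial.

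**What to change.** - State as the main analysis a linear mixed model with fixed treatment, period and sequence and a random participant effect, or the equivalent two-period crossover test. Make GNPT minus sham the contrast, and restate the null to match.
- Remove the condition on sample size. If a fallback is wanted, name it and give its criterion in advance.
- Drop the Kolmogorov–Smirnov gate and check model residuals instead.
- Fix one sensitivity analysis: the rank-sum (two-group Kruskal–Wallis) test of group A against group B on within-participant period differences.

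The cost is analysis wording and a little programming. It needs no further patients, visits or data.
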